## Abstract

**Background:**

Pancreatic Stone Protein (PSP) is a protein naturally produced mainly in the pancreas and the gut. There is evidence from experimental and clinical trials that blood PSP levels rise in the presence of inflammation or infection. However, it is not known whether PSP is superior to other established blood tests (e.g. White Blood Count, Neutrophils or C - reactive protein) in predicting appendicitis in patients presenting with abdominal pain and a clinical suspicion of appendicitis at the emergency room.

**Methods/design:**

The PSP Appendix Trial is a prospective, multi-center, cohort study to assess the value of PSP in the diagnostic workup of acute appendicitis. 245 patients will be prospectively recruited. Interim analysis will be performed once 123 patients are recruited. The primary endpoint of the study concerns the diagnostic accuracy of PSP in predicting acute appendicitis and therefore the evidence of appendicitis on the histopathological specimen after appendectomy.

**Discussion:**

The PSP Appendix Trial is a prospective, multi-center, cohort study to assess the value of PSP in the diagnostic workup of acute appendicitis.

**Trial registration:**

ClinicalTrials.gov: NCT01610193; Institution Ethical Board Approval ID: KEKZH- Nr. 2011–0501

## Background

Appendicitis is defined as an inflammation of the vermiform appendix and is a common condition and an urgent surgical illness. It is one of the most common causes of acute abdominal pain and remains a diagnostic challenge. It has variable manifestations and generous overlap with other clinical syndromes. In fact morbidity increases significantly with the diagnostic delay and left untreated, appendicitis has the potential for severe complications, including perforation or sepsis, and may even cause death. Despite diagnostic and therapeutic advancement in medicine, appendicitis still remains a clinical emergency [1].

No single sign, symptom, or diagnostic test exists which accurately confirms an appendiceal inflammation. The classic history of anorexia and periumbilical pain followed by nausea, right lower quadrant (RLQ) pain, and vomiting occurs in only 50% of cases [1,2].

Accepted etiologic factors of appendicitis are appendiceal lumen obstruction and infection. The main therapeutic option still remains the surgical removal of the vermiform appendix even though a few studies promote an antibiotic treatment [3]. After admission to the emergency department (ED), patients presenting with abdominal pain caused by a variety of different etiologic factors have to be worked up with the goal of approaching 100% sensitivity for the diagnosis in a time-, cost-, and consultation-efficient manner [4].

It is reported that appendectomy carries a complication rate of up to 15%, as well as increased associated costs and the discomfort of hospitalisation and surgery [5]. Delay in diagnosis and treatment account for much of the associated mortality and morbidity. Therefore, the goal of the surgeon is to diagnose appendicitis as early as possible.

The overall mortality rate of 0.2 - 0.8% is attributable to complications of the disease rather than to surgical interventions [2]. The mortality rate in children ranges from 0.1% to 1%; in patients older than 70 years, the rate rises above 20%, primarily because of diagnostic and therapeutic delay [4,6].

## Methods/design

The PSP Appendix Trial is a prospective, multi-center, cohort study to assess the value of PSP in the diagnostic workup of acute appendicitis. Two hundred and forty five patients will be recruited. Interim analysis will be performed once 123 patients are recruited [ Additional file 1]. A power analysis will be performed on the actual and precise data collected. At interim analysis the potential need to modify the sample size will be investigated. If any changes are suggested by the external data monitoring committee, the principal investigators will decide on the feasibility of the potential changes and submit a formal addendum to the ethics committee. No changes will be made to the protocol or study design unless first approved by the ethics committee. Any changes to the protocol approved by the ethics committee will be updated at clinicaltrials.gov [NCT01610193].

### Study objectives

The primary endpoint of the study is histopathological diagnosis of appendicitis on the specimen after appendectomy in order to assess the diagnostic accuracy of PSP calculated in predicting acute appendicitis. Secondary endpoints concern:

1. Grade of appendicitis detected intraoperatively:

G0: Appendix without any abnormalities detected introperatively

G1: Acute appendicitis

G2: Gangrenous appendicitis

G3: Perforated or phlegmon

G4: Periappendicular abscess

2. Alvarado Score elements which are obtained from the patient’s history, the physical examination and from laboratory tests. A score below 5 is strongly against a diagnosis of appendicitis, while a score of 7 or more is strongly predictive of acute appendicitis. In patients with an equivocal score of 5 or 6, a CT scan is used to further reduce the rate of negative appendectomy [10].

3. Pancreatic Stone Protein (PSP) blood serum/plasma levels will be correlated with this score. Surgical complications defined according to the Clavien-Dindo Classification will be monitored [11].

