### Inclusion criteria

All patients that will present at the emergency department with abdominal pain and a clinical suspicion of acute appendicitis:

Age >18 years of age

Clinical suspicion of appendicitis as the primary or differential diagnoses

Patients able to provide informed consent

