### Data collection and statistics

The assessment for patient recruitment starts in the very beginning as soon as the patient attends the emergency room (ER), receives a consultation and a doctor’s assessment of the patient’s condition Additional file 2. If there is a clinical suspicion of appendicitis, the patient should be assessed for eligibility (inclusion and exclusion criteria) to participate in the PSP Appendicitis Trial Additional file 3. If any patient is assessed for eligibility of inclusion in this trial but was found to meet any of the exclusion criteria, the reason and explanation of the exclusion should be also documented in the Clinical Trial Management System (CTMS) https://www.PSPtrail.com[12].

Once a patient is assessed for eligibility and is found to meet the inclusion criteria, the patient should immediately enter the trial before any investigations have ordered blood tests, imaging, etc. The consent forms and patient information have to be provided to the patient. If the patient does not agree to participate in the trial, this should be documented in the online CTMS. If the patient agrees to participate in this trial, blood has to be taken for Pancreatic Stone Protein (PSP) measurement (1 tube of 5-10 ml, for serum determination in clinical chemistry). This tube has to be labelled as B1 followed by the patient trial number (B1_II_YYYY). The letter “B” stands for blood” and “1” as the first blood collection. The patient trial number should be the name initials (II) followed by the year of birth (YYYY). As part of the standard care, blood has to be taken for analysis for full blood count and CRP measurement at participating institutions. In particular, the White Blood Cell Count (WBC), Neutrophil Granulocytes (%) and C-reactive Protein (CRP) will have to be entered into the CTMS. The blood has to be taken at the same time for PSP, WBC and CRP as soon as the patient signs the consent form while still at the emergency department. A pregnancy test (beta hCG) has to be also performed and information entered into the CTMS. The investigators are free to perform any other blood tests deemed necessary.

The investigators are free to use any kind of imaging as part of the routine management of patients. Ultrasound Scan (USS) or Computed Tomography (CT) data will be entered in the CTMS.

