The physician will then decide whether the patient should be subject to further diagnostics, referred to another inpatient or outpatient department or be discharged home [ Additional file 4]. If the patient is admitted for an operation, this has also to be documented in the CTMS. If the physician decides to take blood to assess the progress of the patient before an operation or discharge, an additional tube for PSP measurement is taken (see above). This tube has to be labelled as (B2_II_YYYY, e.g. B2_DR1978, see example above, “2” stands for second blood test for PSP). The same centrifugation process has to be performed to sample B2 as for B1.

Then the investigators will be asked to indicate the type of the operation and the intra-operative findings, if the patient was operated. During hospitalisation, the physician should document any complication according to the Clavien-Dindo Classification of surgical complications. For the patients that were operated, the physician will need to document the date of discharge. Once the histopathology report of the resected specimen has been received, the diagnosis will be entered in the CTMS. To ensure standardized reporting, all centers will adhere to the above classification of appendicitis.

Continuous variables will be compared with the Student t, Mann–Whitney U, one-way ANOVA, and Kruskal-Wallis tests, where appropriate. Differences among proportions derived from categorical data will be compared using the Fischer’s Exact or the Pearson χ^2^ tests, where appropriate. All p values will be two-sided and considered statistically significant if p ≤ 0.05. Sensitivity, specificity, accuracy, positive predictive value (PPV), negative predictive value (NPV), positive likelihood ratio (PLR), negative likelihood ratio (NLR), Yuden’s index (YI), diagnostic odds ratio (OR), and the receiver operator characteristic (ROC) curve will be calculated. Data will be presented as mean (SD), median (i.q.r.) and Odds Ratios (95% CI) where appropriate. Reproducibility of PSP measurements will be performed by duplicating the samples and the variability assessed by the Pearson’s Correlation Coefficient. Statistical analysis will be performed using SPSS Statistics version 20 (SPSS: An IBM Company, Chicago IL, 2011).

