## Discussion

The surgeon’s aim is to correctly diagnose the appendicitis and therefore to minimize the negative appendectomy rate without increasing the incidence of perforation [13]. He has to evaluate a diverse group of patients who present at the ED with abdominal pain and has to consider different aetiologies [14]. The goal of a diagnostic accuracy approaching 100% sensitivity and specificity should be reached in a time-, cost-, and consultation-efficient manner [4].

The overall mortality rate of 0.2-0.8% is attributable to complications of the disease rather than to surgical interventions [2]. The mortality rate in children ranges from 0.1% to 1%; in patients older than 70 years, the rate rises above 20%, primarily because of diagnostic and therapeutic delay [4,6]. Since delayed diagnosis and treatment accounts for much of the mortality and morbidity associated with appendicitis, it is the goal of the surgeon to make an accurate diagnosis as early as possible. False positive diagnosis leads to unnecessary operations which are estimated at 5-15%, while false negative diagnosis may lead to a delay that increases the chances for perforation, peritonitis and sepsis.

Keeping in mind, that appendectomy carries a complication rate of up to 15%, as well as associated costs and the discomfort of hospitalization and surgery, a reliable diagnostic tool such as blood test would be of utmost advantage [5].

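### All suspected cases are enrolled, but the only stated reference standard is histology of a removed appendix, so accuracy and the PSP-versus-WBC/CRP comparison are open to partial-verification bias

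*Protocol article*

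**What the plan says.** **Who enters.** Under Inclusion criteria the cohort is "All patients that will present at the emergency department with abdominal pain and a clinical suspicion of acute appendicitis". It is enough that appendicitis is one possibility: "Clinical suspicion of appendicitis as the primary or differential diagnoses". Under Data collection and statistics, "the patient should immediately enter the trial before any investigations have ordered blood tests, imaging, etc". Entry therefore precedes any decision to operate.

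**What can happen next.** The same section lets the physician order further diagnostics, admit for operation, or have the patient "referred to another inpatient or outpatient department or be discharged home".

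**What counts as disease.** Study objectives: "The primary endpoint of the study is histopathological diagnosis of appendicitis on the specimen after appendectomy". The Abstract describes the endpoint in the same way, as "the evidence of appendicitis on the histopathological specimen after appendectomy". Data collection and statistics gives the route by which the result is recorded: "Once the histopathology report of the resected specimen has been received, the diagnosis will be entered in the CTMS". The article states no reference diagnosis for a patient without a specimen, and no rule for excluding or classifying such a patient.

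**What will be estimated.** Data collection and statistics lists the full set of accuracy measures, including specificity, NPV, likelihood ratios and the ROC curve. The Background adds a comparison of PSP with established markers, and puts the question in patients who present with pain and suspicion, not in patients selected for surgery.

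**The concern.** Accuracy measures need a disease status for each patient analysed. Here that status is available, as stated, only after an appendectomy, and the choice to operate is not random. Blood count and CRP are standard care at the participating sites, and Study objectives notes that laboratory results enter the Alvarado score. The comparators can therefore help decide who is verified. PSP is described only as a trial measurement.

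Two things are at stake. First, the accuracy reported may not be the accuracy in the emergency work-up that the trial says it addresses. Second, verification may be tied more closely to WBC and CRP than to PSP, so the comparison between markers can be distorted even if all are equally good.

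**Working it through.** **1. The plan's own figure.** The sample size of 245 cannot be reproduced, because the article gives no power, target accuracy or prevalence. The point does not depend on it.

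**2. Direction of the bias in operated patients (closed form).** Let Se and Sp be the true values for one test. Let v1 and v0 be the probabilities of operation in test-positive and test-negative patients, taken as equal for those with and without appendicitis. Then

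- observed sensitivity = Se·v1 / [Se·v1 + (1−Se)·v0]
- observed specificity = Sp·v0 / [Sp·v0 + (1−Sp)·v1]

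With assumed Se = 0.80 and Sp = 0.70:

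| v1 / v0 (assumed) | Observed sensitivity | Observed specificity |
|---|---|---|
| 0.80 / 0.60 | 0.64/0.76 = 0.84 | 0.42/0.66 = 0.64 |
| 0.90 / 0.50 | 0.72/0.82 = 0.88 | 0.35/0.62 = 0.57 (0.565) |
| 0.90 / 0.30 | 0.72/0.78 = 0.92 | 0.21/0.48 = 0.44 |

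Sensitivity rises and specificity falls as surgery follows the test more closely.

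**3. Effect on the comparison (simulation).** Assumptions: PSP and WBC have the same true AUC of 0.76. Surgery depends on WBC and the clinical picture, not on PSP. Prevalence is 0.40, 0.60 or 0.75, and the within-group correlation of PSP with WBC is 0, 0.3 or 0.5. There are 600,000 patients per scenario. At prevalence 0.60 and correlation 0.3, 45% are operated on and 10.6% of operations are negative, which is inside the article's 5-15%:

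| Handling of non-operated patients | AUC PSP | AUC WBC | PSP − WBC |
|---|---|---|---|
| True status known for all | 0.76 | 0.76 | 0 |
| Dropped (operated only) | 0.726 | 0.647 | 0.726 − 0.647 = +0.08 |
| Counted as negative | 0.707 | 0.786 | 0.707 − 0.786 = −0.08 |

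Over all nine scenarios the false PSP advantage is about 0.06-0.12 when non-operated patients are dropped. The false WBC advantage is about 0.05-0.14 when they are counted as negative. With zero correlation, PSP's own specificity in operated patients is unbiased, but the comparison is still distorted because WBC's falls.

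These runs leave about 33% of appendicitis unoperated, which is deliberately strong, and at prevalence 0.40 about 21% of operations are negative, outside the article's range. They show that the sign depends on the handling. They do not estimate the size.

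**4. Verified negatives in an operated-only analysis.** The Discussion says: "False positive diagnosis leads to unnecessary operations which are estimated at 5-15" (per cent). If all 245 were operated on, 245 × 0.05 = 12.25 and 245 × 0.15 = 36.75, so about 12 to 37 patients without appendicitis would have histology. The Wilson 95% intervals for an assumed specificity of 0.80 are:

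- 12 patients: 0.52-0.94
- 37 patients: 0.65-0.90

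These counts are upper limits. If 60% were operated on (assumed), they become 245 × 0.60 × 0.05 = 7.4 and 245 × 0.60 × 0.15 = 22.1. With about 7 patients the interval is 0.44-0.95.

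**The case against.** The strongest reply is that this is a condensed article. It cites additional files on recruitment and at the very point where patients are discharged or referred. Those files, or a full protocol, might define follow-up for non-operated patients. That stands as a limit: one can say that the article states no other reference standard, not that none exists. It does not remove the point. The article fixes the primary endpoint, in the Abstract and in Study objectives, in a form that part of its own cohort cannot have.

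A second reply also stands. No analysis set is given, so it does not follow that the accuracy tables must use operated patients only. A reader might infer that the design will produce a false superiority of PSP. The document does not support that: the bias favours PSP if non-operated patients are dropped, but can favour WBC/CRP if they are counted as negative. The second distortion comes only from appendicitis that was never operated on, so it would be small if such cases are rare.

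Third, the size is not in the document. The operated share, prevalence, correlations and true accuracy are all assumed above. The article calls surgical removal the main treatment and leaves imaging free, so scenarios with a large share of appendicitis unoperated are hard to defend. A reader might also infer that many patients will not be operated on. The article foresees such patients but gives no number.

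**Conclusion.** The point holds as a mismatch in the text. The enrolled population is all suspected cases, the stated reference standard covers only those operated on, and the planned measures and marker comparison are claimed for the wider group. Sensitivity, specificity, NPV, likelihood ratios, ROC results and the comparison with WBC/CRP are open to partial-verification bias. For operated-only results the expected pattern is inflated sensitivity and lowered specificity, stronger for WBC/CRP. This rests on routine laboratory results influencing the decision to operate, which the article makes likely but does not quantify.

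Neither the net direction of the marker comparison nor its size can be derived. The only figures tied to the article are the 12 to 37 verified negatives and their wide intervals, and these apply only if operated patients alone are analysed. The matter should be settled while data are being collected, because an analysis plan cannot supply follow-up that was never obtained.

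**What to change.** Define the primary reference standard for every enrolled patient:

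- **Operated:** histology of the specimen.
- **Not operated:** classed as not appendicitis if there is no subsequent appendectomy or appendicitis diagnosis within a fixed window (for example 30 days), established by phone call or record check and entered in the CTMS.
- **Safeguard:** the follow-up status is determined without using PSP, WBC or CRP. Otherwise a routine diagnosis could build the comparators into the reference.

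Make all enrolled patients the primary analysis set. Report the operated-only analysis as secondary, labelled *accuracy among patients undergoing appendectomy*. A verification-bias-corrected analysis (Begg-Greenes or multiple imputation) can serve as a sensitivity analysis, with its assumption stated: that verification depends only on recorded variables. It does not replace follow-up.

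The cost is one protocol amendment, for which Methods/design already describes the route through the ethics committee, a CTMS field, and a short contact or record check per non-operated patient. The downside is a reference less certain than histology in those patients.

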### Inclusion criteria

All patients that will present at the emergency department with abdominal pain and a clinical suspicion of acute appendicitis:

Age >18 years of age

Clinical suspicion of appendicitis as the primary or differential diagnoses

Patients able to provide informed consent

### Exclusion criteria

Age <18 years of

Abdominal discomfort without tenderness or rebound or clinical suspicion of appendicitis

Pregnancy

Patients with impaired consciousness

Patients not able to provide informed consent (Non-German Speakers)

Patients that will receive an appendectomy as part of another elective procedure

Patients who are unable to understand the study purpose.

Family members of study investigators or employees of the participating centers

### Participating surgeons and clinics

Doctors in the Emergency Room who have the first contact with the patients are interns, junior and senior residents as well as chief residents and attending surgeons of the Department of Surgery. Operating surgeons are senior residents, chief residents, attending surgeons as well as consultant surgeons. Participating centers are the Division of Visceral and Transplantation Surgery of the University Hospital Zurich as well as affiliated clinics in Switzerland. Several European hospitals will be participating in this trial as well.

### Data collection and statistics

The assessment for patient recruitment starts in the very beginning as soon as the patient attends the emergency room (ER), receives a consultation and a doctor’s assessment of the patient’s condition Additional file 2. If there is a clinical suspicion of appendicitis, the patient should be assessed for eligibility (inclusion and exclusion criteria) to participate in the PSP Appendicitis Trial Additional file 3. If any patient is assessed for eligibility of inclusion in this trial but was found to meet any of the exclusion criteria, the reason and explanation of the exclusion should be also documented in the Clinical Trial Management System (CTMS) https://www.PSPtrail.com[12].

Once a patient is assessed for eligibility and is found to meet the inclusion criteria, the patient should immediately enter the trial before any investigations have ordered blood tests, imaging, etc. The consent forms and patient information have to be provided to the patient. If the patient does not agree to participate in the trial, this should be documented in the online CTMS. If the patient agrees to participate in this trial, blood has to be taken for Pancreatic Stone Protein (PSP) measurement (1 tube of 5-10 ml, for serum determination in clinical chemistry). This tube has to be labelled as B1 followed by the patient trial number (B1_II_YYYY). The letter “B” stands for blood” and “1” as the first blood collection. The patient trial number should be the name initials (II) followed by the year of birth (YYYY). As part of the standard care, blood has to be taken for analysis for full blood count and CRP measurement at participating institutions. In particular, the White Blood Cell Count (WBC), Neutrophil Granulocytes (%) and C-reactive Protein (CRP) will have to be entered into the CTMS. The blood has to be taken at the same time for PSP, WBC and CRP as soon as the patient signs the consent form while still at the emergency department. A pregnancy test (beta hCG) has to be also performed and information entered into the CTMS. The investigators are free to perform any other blood tests deemed necessary.

The investigators are free to use any kind of imaging as part of the routine management of patients. Ultrasound Scan (USS) or Computed Tomography (CT) data will be entered in the CTMS.

The physician will then decide whether the patient should be subject to further diagnostics, referred to another inpatient or outpatient department or be discharged home [ Additional file 4]. If the patient is admitted for an operation, this has also to be documented in the CTMS. If the physician decides to take blood to assess the progress of the patient before an operation or discharge, an additional tube for PSP measurement is taken (see above). This tube has to be labelled as (B2_II_YYYY, e.g. B2_DR1978, see example above, “2” stands for second blood test for PSP). The same centrifugation process has to be performed to sample B2 as for B1.

Then the investigators will be asked to indicate the type of the operation and the intra-operative findings, if the patient was operated. During hospitalisation, the physician should document any complication according to the Clavien-Dindo Classification of surgical complications. For the patients that were operated, the physician will need to document the date of discharge. Once the histopathology report of the resected specimen has been received, the diagnosis will be entered in the CTMS. To ensure standardized reporting, all centers will adhere to the above classification of appendicitis.

Continuous variables will be compared with the Student t, Mann–Whitney U, one-way ANOVA, and Kruskal-Wallis tests, where appropriate. Differences among proportions derived from categorical data will be compared using the Fischer’s Exact or the Pearson χ^2^ tests, where appropriate. All p values will be two-sided and considered statistically significant if p ≤ 0.05. Sensitivity, specificity, accuracy, positive predictive value (PPV), negative predictive value (NPV), positive likelihood ratio (PLR), negative likelihood ratio (NLR), Yuden’s index (YI), diagnostic odds ratio (OR), and the receiver operator characteristic (ROC) curve will be calculated. Data will be presented as mean (SD), median (i.q.r.) and Odds Ratios (95% CI) where appropriate. Reproducibility of PSP measurements will be performed by duplicating the samples and the variability assessed by the Pearson’s Correlation Coefficient. Statistical analysis will be performed using SPSS Statistics version 20 (SPSS: An IBM Company, Chicago IL, 2011).

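### Pearson's correlation is the only statistic named for the variability of duplicate PSP measurements; it cannot show systematic bias and does not give the size of the error

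*Protocol article*

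**What the plan says.** The protocol article deals with measurement error of the index test in one sentence, under Data collection and statistics: "Reproducibility of PSP measurements will be performed by duplicating the samples and the variability assessed by the Pearson’s Correlation Coefficient". The sentence names a design (duplicates), a target (variability) and one statistic. The article mentions no CV, within-sample SD, limits of agreement, intraclass correlation or concordance coefficient for PSP, and sets no acceptable level of reproducibility.

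The same section plans measures that classify patients by their PSP value, beginning with "Sensitivity, specificity, accuracy, positive predictive value (PPV), negative predictive value (NPV" and going on to likelihood ratios, Youden's index and the ROC curve. No PSP cut-off is fixed in advance.

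**The concern.** Duplicates are two readings of one quantity on one scale. The natural question is how far apart they lie, in PSP units or as a percentage. Pearson's r answers a different question: how closely the pairs follow some straight line, whatever its intercept and (positive) slope. The statistic named therefore does not measure the target named. Because the method is stated, this is not a detail left to an analysis plan that is not shown.

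What is at stake is how a PSP cut-off can be read. Whether a patient near the cut-off would change category on a repeat measurement depends on the error at that level, in units or as a CV. A report that gave only r would not supply that figure.

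**Working it through.** **Inputs.** From the article: the statistic (Pearson's r), the design ("by duplicating the samples") and, only as the number of pairs in one simulation, the planned recruitment of 245. The article states no target r, CV or limit of agreement, so there is no figure to reproduce. All PSP distributions and error sizes below are assumptions.

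**Step 1: bias.** For any constant a and any b > 0, r(x, a + by) = r(x, y). A constant or proportional shift leaves r unchanged. This is algebra and needs no assumption about PSP. If every second reading were exactly 30% above the first, r would be 1.00.

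**Step 2: random error.** With no bias and equal error variances, r = SDb² / (SDb² + SDw²), where SDb is the between-patient SD and SDw the error SD. Hold SDw at 3 units, so that the 95% limits of agreement are ±1.96 × √2 × 3 = ±8.3 throughout, and vary SDb:

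| SDb | r |
|---|---|
| 2 | 4/13 = 0.308 |
| 5 | 25/34 = 0.735 |
| 10 | 100/109 = 0.917 |
| 20 | 400/409 = 0.978 |

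The same assay error gives an r anywhere from 0.31 to 0.98, depending only on who was recruited.

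**Step 3: both together.** Assume log-normal PSP with between-patient log-SD 0.8 (variance 0.64) and a second reading 1.3 times too high. The log error variance is v = ln(1 + CV²). On the log scale r = 0.64 / (0.64 + v). On the raw scale r = (e^0.64 − 1) / (e^(0.64 + v) − 1). The central 95% of duplicate ratios is 1.3 × exp(±1.96√(2v)).

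| CV | v | r (log) | r (raw) | 95% of ratios |
|---|---|---|---|---|
| 10% | 0.00995 | 0.985 | 0.979 | 0.99 to 1.71 |
| 20% | 0.0392 | 0.942 | 0.922 | 0.75 to 2.25 |
| 30% | 0.0862 | 0.881 | 0.840 | not computed |
| 40% | 0.1484 | 0.812 | 0.747 | not computed |

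A simulation under the same assumptions gave 0.985, 0.942, 0.881 and 0.811 (log) and 0.979, 0.922, 0.840 and 0.744 (raw). Without the bias every r in the table would be the same, and the 10% row would have ratios exp(±0.277) = 0.76 to 1.32.

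**Step 4: second simulation, other assumptions.** 245 pairs, median 15 arbitrary units, log-SD 0.6, 5% measurement CV:

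| Second reading | r | Lin's concordance | Mean difference | 95% limits | Within-sample CV |
|---|---|---|---|---|---|
| no bias | 0.991 | 0.991 | −0.1 | −2.9 to 2.7 | 6% |
| +5 units | 0.991 | 0.893 | 4.9 | 2.1 to 7.7 | 19% |
| × 1.5 | 0.991 | 0.773 | 8.2 | −2.5 to 18.8 | 34% |
| × 2 | 0.991 | 0.534 | 16.4 | −4.4 to 37.2 | 56% |

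The within-sample CV and the limits respond to the bias; r does not move.

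**The case against.** The best defence is that r is not blind to random error. In step 3 it falls from 0.985 to 0.81 on the log scale, and from 0.979 to about 0.75 on the raw scale, as CV rises from 10% to 40%. If the duplicates are interchangeable replicates of one sample, most of their error is random, which is the part that r partly reflects. The article describes no difference in run, plate or laboratory that would shift every second reading, and the B1 and B2 tubes are serial draws that it does not call duplicates. The 30% bias is thus an illustration, not a forecast. This stands. It does not rescue r, because step 2 shows that even without bias r confounds assay error with patient spread and gives no error size.

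A reader might also infer that the trial would declare the assay reproducible on a statistic that could not show otherwise. The article does not support that: it states no threshold or acceptance rule, and a poor assay would lower r.

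Nor does it follow that the diagnostic result is compromised. The choice of reproducibility statistic changes no patient's PSP value, and hence neither the ROC curve nor the sensitivity or specificity at any cut-off.

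Finally, an absolute-agreement intraclass correlation is not a full remedy. In step 3 at 10% CV it is 0.64 / (0.64 + 0.00995 + (ln 1.3)²/2) = 0.935, which also looks reassuring, because it too depends on between-patient spread.

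**Conclusion.** The sentence is wrong as written: it assigns to Pearson's r the assessment of variability, and r does not measure it. Blindness to constant and proportional bias is exact and rests on no assumption. The dependence on between-patient spread follows from the formula in step 2, given equal, independent errors. The numerical sizes (r of about 0.98 with ratios of 0.99 to 1.71; r of 0.92 to 0.94 with ratios of 0.75 to 2.25) rest on the assumed log-SD of 0.8, the assumed 30% bias and CVs of 10% and 20%, and would differ with real PSP data.

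Severity is minor to moderate. Reproducibility is a supporting assay analysis; the primary ROC analysis and the sample size of 245 stay as they are.

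**What to change.** Replace Pearson's correlation in that sentence with:

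- the within-sample CV (or within-sample SD) from the duplicates;
- the Bland-Altman mean difference with 95% limits of agreement, computed on log PSP and reported as ratios if error grows with level.

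The mean difference is informative only if first and second readings are distinguishable, for example by order or run, so the sentence should say how they are labelled. An absolute-agreement intraclass correlation may be added, with the caveat that it also depends on between-patient spread; it should not lead.

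The cost is one sentence. The same duplicates are used, with no further samples or patients.
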